### Objective and hypothesis

The primary aim of this multicenter trial is to assess whether RIVP combined with ACP leads to better outcomes than ACP alone for patients undergoing TARS under moderate hypothermia (Protocol no. 1.0, dated 10 January 2018). We hypothesize that combining RIVP with ACP will lead to lower incidences of mortality, major complications and postoperative temporary neurological defects than ACP alone, as well as shorter duration of ventilation and stay in the intensive care unit (ICU). The results of this trial will serve as a foundation for future clinical recommendations regarding the application of RIVP in TARS and should potentially improve treatment.

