Secondary outcomes will include the proportion of patients with a stroke/cerebrovascular incident, paraparesis, postoperative prolonged intubation (> 48 h), temporary neurological deficit, myocardial infarction (MI), acute kidney injury not requiring dialysis, surgical re-exploration for bleeding, and deep sternal wound infection. Patients who require assistance to stand or to walk will be defined as having paraparesis (Tarlov score 3–4) [39]. Temporary neurological deficit [40] will be defined as the occurrence of postoperative agitation, confusion, delirium, obtundation, or a transient focal neurological deficit (resolution within 72 h) without any evidence of new structural abnormality on computed tomography or magnetic resonance imaging. Myocardial infarction [41] will be defined as a rise and/or fall of cardiac troponin values at least one value above the 99th percentile upper reference limit and at least one of the following: symptoms of myocardial ischemia, new ischemic electrocardiogram (ECG) changes, development of pathological Q waves, imaging evidence of new loss of viable myocardium or new regional wall motion abnormality in a pattern consistent with an ischemic etiology, or the identification of a coronary thrombus by angiography or autopsy (but not for type 2 or 3 MI). Prolonged intubation will be defined as a requirement of intubation lasting more than 48 h.

Tertiary outcomes include the length of ICU stay, length of hospital stay, length of endotracheal intubation, volume of perioperative blood product transfusions, as well as total hospitalization cost. The proportion of patients who develop postoperative ascites will serve as a measure of safety in this trial.

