### Sample size calculation

The sample size was calculated based on the primary outcome of our unpublished pilot study (manuscript in preparation), carried out at West China Hospital (Biomedical Ethics Committee approval no. 201824). In this study, we included 76 patients (*n* = 38 in each group), and defined the primary outcome as the abovementioned 30-day composite of operative mortality and major complications. In this pilot study, 13 of 38 control patients (34.2%) suffered the following outcomes: death, 4; paraplegia, 1; postoperative renal failure, 7; severe liver dysfunction, 4; or gastrointestinal complications, 1. A total of 9 of 38 patients in the RIVP group (23.7%) experienced the following outcomes: death, 3; paraplegia, 0; postoperative renal failure, 6; severe liver dysfunction, 1; or gastrointestinal complications, 1. The trial is planned to have 80% test power with a two-sided type I error rate of 5%, assuming a dropout rate of 10% over the course of the entire study. For statistical significance, 636 patients (318 participants in each arm) will be required for this trial according to the following statistical formula not including the 76 patients in the pilot study:$$ \mathrm{n}=\frac{{\left({Z}_{1-\alpha /2}+{Z}_{1-\beta}\right)}^2\left[{p}_1\left(1-{p}_1\right)+{p}_2\left(1-{p}_2\right)\right]}{\delta^2} $$

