### Data analysis

All patients will be analyzed according to the intention-to-treat protocol. Data analysis will be performed by a statistician using SPSS 20.0 (IBM, Chicago, IL, USA). Differences associated with *p* < 0.05 will be considered statistically significant. Continuous variables will be expressed as mean ± standard deviation or median (interquartile range), and differences in such variables will be analyzed using an independent *t* test or the Wilcoxon signed-rank test, depending on whether data are normally distributed. Categorical variables will be described as numbers (percentages), and differences in such variables will be analyzed using a *chi-square test* and *Fisher’s exact test*. *Kaplan-Meier* curves and *log-rank* analysis will be used to compare inter-group differences in primary and secondary outcomes. Univariate and multivariate logistic regression will be performed to determine relative risk of primary and secondary outcomes in the RIVP group compared with the control group.

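### ICU stay, hospital stay and intubation time are compared over all patients with no rule for death, so any mortality difference between arms distorts them, in a direction that depends on when deaths occur

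*Protocol article*

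**What the plan says.** In the protocol article, Study outcomes lists the three durations as plain lengths: "Tertiary outcomes include the length of ICU stay, length of hospital stay, length of endotracheal intubation". It does not restrict them to survivors, convert them to days free of ICU or ventilator, or give a value for a patient who dies. The same section makes prolonged intubation a secondary outcome: "Prolonged intubation will be defined as a requirement of intubation lasting more than 48 h".

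Data analysis sets the population, "All patients will be analyzed according to the intention-to-treat protocol", and gives continuous variables an independent t test or the "Wilcoxon signed-rank test, depending on whether data are normally distributed". Kaplan-Meier and log-rank methods are reserved for other endpoints: this "analysis will be used to compare inter-group differences in primary and secondary outcomes". The tertiary durations are not covered by that sentence.

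Objective and hypothesis expects that "combining RIVP with ACP will lead to lower incidences of mortality, major complications" and, in the same sentence, "as well as shorter duration of ventilation and stay in the intensive care unit (ICU".

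**The concern.** A patient who dies in the ICU on day 1 has a one-day ICU stay and a short intubation. A plain two-group test reads both as good results. A patient who dies after four weeks in the ICU has a long stay, which the test reads as a bad result. Either way the recorded length mixes speed of recovery with time to death. If the arms differ in mortality, as the trial hopes, they differ in how many such lengths they contain, even when RIVP has no effect on recovery.

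At stake is the stated hypothesis on ventilation and ICU stay. A difference, or the lack of one, could not be read as an effect on recovery. Prolonged intubation has a related gap: a patient who dies intubated before 48 h can never meet the definition and is counted as free of the event.

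**Working it through.** **Inputs from the protocol**

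- Arm size: 318. This reproduces from the protocol's formula: (1.960 + 0.842)² × (0.342 × 0.658 + 0.237 × 0.763) / 0.105² = 288.9, so 289; 289 × 1.10 = 318 per arm, 636 in total. It has no other bearing here. The protocol gives no figure for the durations.
- Pilot deaths (Sample size calculation): control "suffered the following outcomes: death, 4; paraplegia, 1", so 4/38 = 10.5%; RIVP 3/38 = 7.9%. In 318 patients that is 33.5 and 25.1 expected deaths.
- Published 30-day mortality with ACP + MHCA (Background): 5.3–19%.

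**Assumptions, because the protocol gives neither**

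- Stay without death: lognormal, median 5 days, log SD 0.7 or 0.8, identical in both arms.
- Time of death: varied below.
- Mortality contrasts other than the pilot's: 15% vs 8%, 19% vs 9.5% and 19% vs 5.3% (the last pairs the two ends of the published range).

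**What sets the sign**

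Let m be mortality, S the mean stay without death and D the mean time to death. The mean recorded stay in an arm is (1 − m)S + mD. With no true effect on stay:

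RIVP − control = (m_control − m_RIVP) × (S − D)

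The arm with more deaths looks shorter if D < S and longer if D > S. With log SD 0.7, S = 5 × exp(0.7²/2) = 6.39 days. Results in days, with simulated values in brackets:

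| Mortality, control vs RIVP | Deaths days 0–2 (D = 1) | Days 0–14 (D = 7) | Days 7–30 (D = 18.5) |
|---|---|---|---|
| 10.5% vs 7.9% | +0.14 (+0.15) | −0.02 (−0.03) | −0.32 (−0.31) |
| 19% vs 9.5% | +0.51 (+0.52) | −0.06 (−0.07) | −1.15 (−1.15) |
| 19% vs 5.3% | +0.74 (+0.73) | −0.08 (−0.09) | −1.66 (−1.66) |

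**False findings, rank-sum test, same model**

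Share of 1,500 trials significant with control shorter / with RIVP shorter (nominal 2.5% each):

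| Mortality | Days 0–2 | Days 0–14 | Days 7–30 |
|---|---|---|---|
| 10.5% vs 7.9% | 8.5% / 0.9% | 2.9% / 2.3% | 0.9% / 8.3% |
| 19% vs 9.5% | 49.9% / 0.0% | 0.9% / 5.3% | 0.0% / 43.8% |
| 19% vs 5.3% | 80.5% / 0.0% | 0.9% / 6.4% | 0.0% / 74.9% |

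**Second stay model (log SD 0.8), separate runs**

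| Time of death | 10.5% vs 7.9% | 15% vs 8% |
|---|---|---|
| Mean 2 days: control falsely shorter | 4.8–6.4% | 17.3–19.1% |
| Mean 5 days: control falsely shorter | 3.4–3.5% | 5.0–6.2% |
| Mean 7 days: control falsely shorter | 3.4% | 3.0% |
| Uniform, days 0–14: control falsely shorter | 2.0% | 1.5% |
| Uniform, days 7–30: RIVP falsely shorter | 7.1–7.5% | 23.6–24.9% |

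The rank-sum test is used because the arms are independent. The signed-rank test named in Data analysis is for paired data.

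**The case against.** The strongest reply is that a condensed article need not say how a death is coded for a tertiary outcome. Its one sentence on continuous variables is generic, and no sentence says that death counts as discharge or extubation. It is true that the coding is inferred. But the article does fix the form of the outcome, the population and the test, and it names time-to-event methods only for other outcomes. Following those statements gives the comparison examined here.

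The second reply is that size and direction rest on assumed stays and death times. That stands, and it is why the result is given as a range. The 15% vs 8% contrast appears nowhere in the protocol, and the pilot arms were one death apart.

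Third, a reader might infer that ranking deaths worst would greatly raise the power to show a shorter stay. The numbers do not support that. With no difference in stay at all, worst-rank scoring favours RIVP in about 6–9% of trials at pilot mortality and in 31% at 15% vs 8%, because it tests mortality as well. With a stay about 14% shorter under RIVP among survivors, a survivors-only test already has about 58% power. The reason for the change is a clear interpretation, not power.

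Fourth, prolonged intubation is a secondary outcome, so the t test and Wilcoxon rule does not govern it and Kaplan-Meier methods are named. That is correct. However, those methods do not count a death before 48 h as an event unless the plan says so, so the gap remains.

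**Conclusion.** The point holds in conditional form. As written, the three duration comparisons are distorted by any mortality difference between arms, and the trial expects one. At pilot mortality the distortion is small: about 0.15 days in the mean if deaths fall in days 0–2, with a false finding for control in roughly 5–9% of trials across the two early-death models. It grows with the mortality difference, is near nil if deaths spread over days 0–14, and reverses if they fall in days 7–30.

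A reader might infer that the plan works against RIVP, or that the arm with more deaths always looks better. The protocol does not support either reading, because it gives neither the timing of deaths nor the distribution of stay. The direction may even differ among the three durations, since each has its own typical length. That the direction is unknown is itself a reason to fix the rule in advance.

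The problem is confined to three tertiary outcomes and one secondary outcome. The primary composite, which already includes death, and the sample size are untouched. Severity is minor to moderate.

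**What to change.** Before unblinding, state one rule for the durations. Either:

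- compare ICU-free, hospital-free and ventilator-free days to day 30, with deaths scored 0; or
- compare the durations by rank-sum test with in-hospital deaths given the worst rank.

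In both cases report mortality by arm next to the result, and give survivor medians as description only. Keep prolonged intubation as defined, and add a supportive analysis of prolonged intubation or death before extubation within 48 h.

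The cost is analysis wording. Follow-up already runs through hospitalisation and to 30 days after surgery for discharged patients, so no new visits are needed. The downside is that the measure combines duration with mortality and is no longer a pure effect on stay. With free days, a survivor still in the ICU or hospital at day 30 also scores 0 for that measure and ties with a death.

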### Monitoring of adverse and clinical events

Intraoperative data will include variables linked to the arterial cannulation site for cerebral perfusion (innominate artery, internal carotid artery, axillary artery, or subclavian artery), duration of HCA, CPB time, warming and cooling time, cross-clamp time, surgery time, temperature at the initiation of hypothermic circulatory arrest, concomitant procedures and the application of cross-clamp to the dissected aorta before initiation of hypothermic circulatory arrest, number of units of packed red blood cells, fresh-frozen plasma, pooled platelets and cryoprecipitate administered perioperatively, the highest lactate value during CPB, and the highest flow and pressure of ACP and RIVP.

Patients will be monitored on a daily basis for 7 days after surgery to collect data on temperature, partial pressure of oxygen (PaO_2_) and carbon dioxide (PaCO_2_), inspired oxygen (FiO_2_), ventilation mode, hemoglobin and leukocyte count, and volume of chest drainage. Symptomatic cardiorespiratory complications and other secondary outcome measures (see above) will also be recorded during routine diagnostic tests. These parameters and the timing of notable events will be tracked until hospital discharge.

Patients will be instructed to visit during the hospitalization or following discharge for postoperative data collection. If a face-to-face appointment is not possible, follow-up will be completed over the phone. During each visit, patient characteristics, including mortality, cardiovascular and cerebrovascular events, postoperative renal and liver function, and gastrointestinal complications, will be recorded, Abdominal ultrasound will also be performed at 7 days postoperatively. In addition, radiology and electrocardiography will be performed at each visit after discharge, uploaded to the database and evaluated by outcome assessors blinded to patient allocation.

Preoperative and postoperative data will be recorded by a member of the research team at each participating center who will be blinded to randomization status and who will not be part of the surgical team that performs the interventions. Intraoperative data will be collected by the study perfusionists and anesthesiologists.

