## Methods

### Study design

This study is designed as a multicenter, randomized controlled, assessor-blind, parallel-group study with a superiority framework. Five clinical research centers in China will participate: West China Hospital of Sichuan University, Second Affiliated Hospital of Nanjing Medical University, First Affiliated Hospital of Wannan Medical University, The Second Xiangya Hospital of Central South University, and First Affiliated Hospital of the University of South China.

A total of 636 participants with type A aortic dissection will be randomly assigned by computer to either the MHCA (control) group or the RIVP group at a ratio of 1:1. Patients assigned to the control group will receive selective ACP alone under moderate hypothermia, while patients in the RIVP group will receive selective ACP combined with RIVP under moderate hypothermia. All patients will be admitted to a cardiovascular ICU after surgery, where they will remain until they are considered stable enough to transfer back to a general unit. Postoperative follow-up will be conducted throughout hospitalization (regardless of length of stay) and for up to 30 days after surgery if the patient is discharged, which will be sufficient to show the prognosis of surgical treatment. Patient enrollment began in January 2019 and is expected to be complete within 3 years thereafter. The following members of the study will be blinded to the patients’ group allocation: patients themselves, outcome assessors, and the statistician.

Perfusionists and surgeons in the trial will be experienced in performing the necessary procedures. Interventions will be carried out intraoperatively. Patients’ medical records will be reviewed for in-hospital complications and medication usage.

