### Study outcomes

The primary outcome will be a composite of operative mortality and major complications, including paraplegia, postoperative renal failure, severe liver dysfunction, and gastrointestinal complications. Operative mortality is defined as any death that occurs in the same hospital in which the surgery was performed. Other complications will be defined according to the Society of Thoracic Surgery (https://www.sts.org/). The primary outcome will be measured throughout hospitalization (regardless of length of stay) and for up to 30 days after surgery if the patient is discharged. The decision to initiate renal replacement therapy (RRT) will be made by experienced staff in the cardiac ICU. Patients are given RRT if they are classified as grade F according to the RIFLE criteria: serum creatinine ≥ 4 mg/dL or an increase of at least threefold in baseline serum creatinine, or > 75% decline in the estimated glomerular filtration rate. Urine output < 0.3 mL/kg/h for 24 h or anuria for 12 h. We have defined RRT as intermittent hemodialysis or continuous venovenous hemofiltration [38].

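### The protocol ends tracking of the secondary outcomes at hospital discharge but runs follow-up to day 30; the window needs reconciling, mainly for late events such as deep sternal wound infection

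*Protocol article*

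**What the plan says.** In the protocol article, the section on monitoring of adverse and clinical events first lists daily measurements for 7 days. It then says: "Symptomatic cardiorespiratory complications and other secondary outcome measures (see above) will also be recorded during routine diagnostic tests". The next sentence sets the end point for all of this: "These parameters and the timing of notable events will be tracked until hospital discharge".

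Three other places bear on the window:

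- Study design: "Postoperative follow-up will be conducted throughout hospitalization (regardless of length of stay) and for up to 30 days after surgery if the patient is discharged".
- Data collection and management: all outcome parameters are to be recorded by the local trial team from enrollment through the whole follow-up period.
- Study outcomes: the primary outcome has the same window as the general follow-up, namely the hospital stay and up to day 30 after surgery for those discharged. The secondary outcomes are listed as proportions with no window of their own.

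The paragraph after the discharge sentence adds a further contact: "Patients will be instructed to visit during the hospitalization or following discharge for postoperative data collection", by phone if a visit is not possible. The items recorded there are described as "including mortality, cardiovascular and cerebrovascular events, postoperative renal and liver function, and gastrointestinal complications". Radiology and electrocardiography are done at each visit after discharge.

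**The concern.** Read plainly, the parameters tracked until discharge include the secondary outcomes named in the sentence before. That is the only explicit window the article attaches to them, and it disagrees with the general follow-up rule and with the data collection rule.

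The conflict matters because discharge happens after randomization and treatment may affect it. Length of hospital stay is itself a tertiary outcome. If an event is looked for only while the patient is in hospital, the arm with the shorter stay has less time in which an event can be recorded. The Data analysis section compares categorical outcomes as simple proportions (chi-square or Fisher's exact test) and by logistic regression, and neither allows for unequal observation time. It also names Kaplan-Meier curves and the log-rank test, but censoring at discharge would be informative, because patients who have recovered leave first.

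**Working it through.** **Step 1. Which outcomes depend on the discharge rule.** The secondary and safety outcomes, set against the post-discharge list and the other sections:

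| Outcome | Covered after discharge in the printed text? | Exposure to the problem |
|---|---|---|
| Stroke / cerebrovascular incident | Yes, cerebrovascular events | Low |
| Myocardial infarction | Yes, cardiovascular events and electrocardiography | Low |
| Acute kidney injury without dialysis | At least partly, renal function | Low |
| Prolonged intubation (> 48 h) | Not named | Low, mainly early |
| Re-exploration for bleeding | Not named | Low, mainly early |
| Temporary neurological deficit | Not named | Low, mainly early |
| Paraparesis | Not named | Possible |
| Deep sternal wound infection | Not named | Clearest case, can appear late |
| Ascites (safety measure) | Abdominal ultrasound at 7 days in both arms | None from this rule |

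**Step 2. What is not touched.** The primary outcome has its own day-30 window in the Study outcomes section. The sample size rests on the primary outcome alone and reproduces from the printed formula. With p1 = 0.342 and p2 = 0.237, n = (1.960 + 0.842)² × [0.342 × 0.658 + 0.237 × 0.763] / 0.105² = 288.9, so 289 per arm. Then 289 × 1.10 = 317.9, which rounds to the stated 318. Nothing in this point changes that figure.

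**Step 3. How large a bias could be.** The documents give no length of stay and no event rates for the secondary outcomes, so this is an illustration. Assumptions: equal true 30-day risk in both arms, only in-hospital events counted, and every patient in an arm discharged on the same day. The pairs of stays (control / RIVP) are assumed to be 16/14, 18/14 and 20/15 days.

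(a) *Constant hazard to day 30.* For a 30-day risk R, λ = −ln(1 − R)/30, and the observed risk by day d is 1 − exp(−λd). For R = 5%:

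- 16/14 days: 0.0237 / 0.0270 = 0.88
- 18/14 days: 0.0237 / 0.0303 = 0.78
- 20/15 days: 0.0253 / 0.0336 = 0.75

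With R = 3% or 10% the ratios are the same to within 0.01. They are close to the ratio of days observed (14/16, 14/18, 15/20).

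(b) *Early events.* Suppose 80% of events fall in the first 7 days and the rest are spread evenly from day 7 to day 30. The observed fraction of events by day d is 0.8 + 0.2 × (d − 7)/23, and R cancels in the ratio:

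- 16/14 days: 0.861 / 0.878 = 0.98
- 18/14 days: 0.861 / 0.896 = 0.96
- 20/15 days: 0.870 / 0.913 = 0.95

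(c) *Direction.* If RIVP patients stayed longer by the same margins, the ratios invert: 16/14 = 1.14, 18/14 = 1.29 and 20/15 = 1.33 for constant hazard (using the days-observed approximation), and 1.02 to 1.05 for early events.

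**The case against.** The strongest reply is that the discharge sentence is a single loose line set against two general rules. Study design carries follow-up to day 30, and Data collection and management applies outcome recording to the whole follow-up period. The post-discharge list is introduced as an inclusion list and need not be complete. The schedule of assessments is a figure that is not shown, so the unnamed items may appear there or on the case report form. This is fair. It means the article does not establish that collection stops at discharge. It does not remove the conflict, and nothing in the visible text tells a site to ask a discharged patient about the sternal wound or leg function.

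Four stronger readings are tempting, and the documents do not support them:

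- *That all secondary complications go unobserved after discharge.* The post-discharge visit or call covers cardiovascular, cerebrovascular and renal events.
- *That the trial will show spuriously fewer complications with RIVP.* The objective section hypothesizes shorter ventilation and ICU stay, but no shorter hospital stay, and no stay data are given. The direction is open.
- *That paraplegia, and so the primary outcome, is compromised.* Paraplegia is absent from the visit list, but the Study outcomes section expressly gives the primary outcome the day-30 window.
- *That the safety comparison is biased.* The named safety measure, ascites, is supported by an ultrasound at a fixed day in both arms. Adverse events are followed to resolution or stabilization, which does not end at discharge.

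**Conclusion.** The point holds as a contradiction about the ascertainment window for the secondary outcomes. If the discharge rule is the one that sites follow, deep sternal wound infection and paraparesis are observed for a time that depends on length of stay. Their proportions may then be biased in either direction. The bias is small for early events (apparent risk ratio about 0.95 to 0.98 in the illustration, or the inverse) and could be material for late ones (about 0.75 to 0.88, or the inverse). Those figures rest entirely on assumed stays and assumed event timing; the true size cannot be computed from the article. The constant-hazard case is the less favorable of the two and suits only outcomes that keep arising up to day 30. The point is still worth acting on, because events that are not asked about after discharge may not be recoverable at the analysis.

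**What to change.** 1. In the section on monitoring of adverse and clinical events, replace the discharge end point, for all secondary outcomes, with recording to 30 days after surgery in every patient, in hospital or discharged. This brings it into line with Study design and with Data collection and management.
2. Add deep sternal wound infection and lower-limb motor function to the items asked at the planned post-discharge visit or call. If the schedule of assessments or the case report form already has them, say so in the text.
3. Compare the arms on secondary outcomes over that fixed 30-day window. Report in-hospital events after day 30 separately, since the present follow-up rule also runs longer for patients with long stays.

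The cost is a wording change and a few case report form items on a contact that is already planned. Some events will be reported by phone and will need confirmation from records.
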